#### Out of Specification product

An Out of Specification (OOS)-product is a product that cannot be made according to the criteria, for example when an insufficient number of chondrons is isolated. In this case, a risk-benefit assessment of implantation of the OOS-product will be done by the treating orthopedic surgeon and qualified person. They will consider alternative treatment options for the patient, whether manufacturing can be (partly) repeated, and the ratio of the cells restored. The OOS-product will contain a higher percentage of MSCs in order to compensate for the missing chondrons, and two million cells per milliliter will be implanted. Patients that receive an OOS-product will not be included in efficacy analyses, but AE, SAE, and SUSARs will still be reported and the patient will be included in safety and cost-effectiveness analyses. Patients will be informed of this OOS-procedure both during the screening visit and through the patient information letter, before signing the informed consent form. The researchers will report implantation of an OOS-product to the Central Committee on Research Involving Human Subjects (CCMO) and Health and Youth Care Inspectorate (IGJ), according to the CCMO guidelines.

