#### Primary exclusion criteria (at the outpatient clinic)

If the patients meet any of the following criteria at the screening visit, they will not be eligible for the study:
Malalignment of > 5° (correctional osteotomy is allowed during the trial).(History of) OA, defined as Kellgren-Lawrence grade ≥ 3 as determined from appropriate radiography.Joint instability (ligament reconstruction is allowed during the trial).Concomitant inflammatory disease that affects the joint (rheumatoid arthritis, metabolic bone disease, psoriasis, gout, symptomatic chondrocalcinosis).(History of) Septic arthritis.(History of) Total meniscectomy in the target knee joint.Any surgery in the index knee joint 6 months prior to study inclusion.Risk groups for MRI due to the magnetic field such as patients with pacemakers, nerve stimulators, metal particles, stents, clips or implants, (possible) pregnancy, or breastfeeding.

Definitive eligibility is assessed during surgery based on the criteria below.

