### Criteria for discontinuing or modifying allocated interventions {11b}

Patients can leave the study at any time for any reason if they wish to do so without any consequences. The patient’s participation in this study can also be ended by the investigator if the patient is uncooperative and/or does not attend study visits. The patient data that have been collected up to that moment will be included in the analysis. In case too many data are missing (e.g., missing baseline or all of the follow-up patient-reported outcome measures (PROMs), study visits, or MRI-scans), the patient will be replaced by a new patient. This study will be prematurely ended in case of any abundance in adverse events or procedure/compound-related complications or if the independent rheumatologist advises this termination. Criteria for study termination include any suspected unexpected serious adverse reaction (SUSAR) or serious adverse event (SAE) based on an allergic reaction and clear allergic or iatrogenic effects in two or more patients including patients which report back to the hospital with serious iatrogenic complaints. In case of premature ending, all included patients will be informed by their treating orthopedic surgeon. In case of illness, patients will be asked to contact the primary investigator. Patients that are discovered during surgery not to meet the criteria will not receive IMPACT and will be treated according to the standard of care, based on the findings during surgery. These patients will be removed from the study. Patient data included up to that moment will be included in the analysis.

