### Implementation {16c}

After signing the informed consent forms, the researchers will use Castor EDC [26] to allocate the patient to one of the study arms. The study group will be revealed at the same time to both the patient and researcher.

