### Methods in analysis to handle protocol non-adherence and any statistical methods to handle missing data {20c}

The primary outcome will be assessed using an intention-to-treat analysis. Missing data will be reduced to a minimum by using the appropriate measures described above. Mixed models do not require imputations for missing data. If any statistical method is needed to account for missing data in the secondary outcomes, multiple imputation will be used.

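### The out-of-specification exclusion contradicts the intention-to-treat primary analysis; with removal for ineligibility at surgery, it thins only the IMPACT arm within the 9-month window

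*Protocol article*

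**What the plan says.** All references are to the protocol article.

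- **Analysis set.** Section {20c}: "The primary outcome will be assessed using an intention-to-treat analysis". The primary outcome is total KOOS, compared between arms up to 9 months after randomisation (Outcomes {12}).
- **OOS product.** The section of that name: "Patients that receive an OOS-product will not be included in efficacy analyses". The same patients stay in the safety and cost-effectiveness analyses.
- **Ineligible at surgery.** Section {11b}: "These patients will be removed from the study", followed by "Patient data included up to that moment will be included in the analysis".
- **Replacement.** Section {11b} also provides that, when too many data are missing, "the patient will be replaced by a new patient". Its examples are "missing baseline or all of the follow-up patient-reported outcome measures (PROMs), study visits, or MRI-scans". This applies to either arm.
- **Timing.** Randomisation is at the baseline visit (Table 1), and the Implementation section {16c} places it directly after consent: "After signing the informed consent forms, the researchers will use Castor EDC". Final suitability is settled later: "Definitive eligibility is assessed during surgery based on the criteria below". Controls may cross over only after 9 months (Trial design {8}).

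**The concern.** An intention-to-treat comparison keeps every randomised patient in the assigned arm. A rule that drops patients from efficacy because of how their product turned out is incompatible with that, since KOOS to 9 months is an efficacy analysis. The two statements cannot both govern the primary result, and as written the choice between them could be made after the data are seen.

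The exclusions also depend on events that only surgery can reveal: lesion size after debridement, undiagnosed osteoarthritic lesions, or too few isolated chondrons. Within the primary window no control has surgery under the protocol, so controls with the same features are not identified and are kept. The trial is open label, and whether an OOS product is implanted is a case-by-case judgement after allocation is known. At stake is whether the phase III primary estimate compares the groups that were randomised. In addition, efficacy and cost-effectiveness would rest on different populations.

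**Working it through.** **1. The plan's own figure.** The Sample size section {14} gives SD 15, correlation 0.7, difference 10, power 0.8, alpha 0.05 and a minimum of 44. A Hotelling-Lawley test of group by time with four assessments (0, 3, 6, 9 months), equal correlations, and a group difference of 0 at baseline and 10 at each follow-up gives 44 in total (power 0.807). Cross-check: change-score SD = 15 × √(2 × (1 − 0.7)) = 11.62, so n per arm = 2 × (1.96 + 0.842)² × 11.62² / 10² = 21.2, rounded up to 22, or 44 in total. At the planned 60 the Hotelling-Lawley power is 0.927. The stated figure is not in dispute.

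**2. Where each rule can act up to 9 months.**

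| Rule | IMPACT arm | Control arm |
|---|---|---|
| OOS product, out of efficacy | yes | no, no product is made |
| Ineligible at surgery, removed | yes | no, no surgery before crossover |
| Replacement for missing data | yes | yes |

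**3. What remains of a patient removed at surgery.** In Table 1, Group A has baseline questionnaires and then questionnaires at 3, 6 and 9 months after surgery. Keeping data up to removal therefore normally keeps the baseline KOOS only. The mixed model then treats the missing follow-up as if it resembled that of IMPACT patients who were followed, although this patient received no implant.

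**4. Power.** Normal approximation, power = Φ(10/SE − 1.96), with SE = 11.62 × √(1/30 + 1/n) and n the IMPACT patients left:
- n = 30: SE 3.00, power 0.915
- n = 27: SE 3.08, power 0.901
- n = 24: SE 3.18, power 0.882

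Lost power is minor. The issue is bias, which the margin from 44 to 60 does not address.

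**5. Illustrative bias.** The article gives no OOS or surgical-ineligibility rate, so everything here is assumed. Let a share p of each arm carry the hidden feature. Those patients gain 0 from allocation to IMPACT, and the rest gain 10.
- Intention-to-treat difference: 10 × (1 − p).
- Difference after one-arm exclusion, with no prognosis gap or a gap that cancels through baseline: 10.
- Inflation: 10 − 10 × (1 − p) = 10p.

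| p | of 30 IMPACT patients | Intention-to-treat | After exclusion | Inflation |
|---|---|---|---|---|
| 5% | 1.5 | 9.5 | 10 | 0.5 |
| 10% | 3 | 9.0 | 10 | 1.0 |
| 20% | 6 | 8.0 | 10 | 2.0 |

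If these patients also have a prognosis d points worse and the contrast does not adjust for it, the result after exclusion is 10 + pd and the inflation is p × (10 + d). For example, p = 10% and d = 10 gives 0.10 × 20 = 2.0 points.

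**6. False-positive rate under similar assumptions.** Suppose the true intention-to-treat difference is zero and the excluded share would have scored 10 points worse than the rest of the arm. The shift is 1.0 point at 10% excluded (SE 3.08) and 2.0 points at 20% (SE 3.18). The two-sided rejection rate becomes about 6.2% and 9.6% instead of 5%.

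**The case against.** Several points on the other side stand and limit the claim.

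- **Removal is not deletion.** A reader might infer that patients ineligible at surgery vanish from the analysis. Section {11b} keeps their data up to removal, so the defect is lost follow-up. Section {18b} also asks for a 9-month online survey where feasible, but it speaks of patients who choose to stop, covers one time point, and does not clearly reach patients removed by the team.
- **Replacement is not shown to breach intention-to-treat.** It applies to both arms, and the Limitations section expects drop-out in the control arm. The text does not say that a replaced patient's data are discarded. What is missing is a statement that the patient stays in the analysis set.
- **The step from 44 to 60 does not make replacement redundant.** That margin also covers uncertainty in the correlation pattern and in the SD for nonsurgical treatment.
- **Direction and size are assumed.** OOS recipients still receive an implant at the same cell concentration, and patients ineligible at surgery receive standard care, so zero gain is not documented. No text links chondron yield to prognosis, and a stable prognosis gap would largely cancel in a baseline-adjusted contrast. However, section {20a} names only treatment group and assessment date as fixed factors and tests the group effect, which read literally would not remove such a gap.
- **Screening limits the numbers.** Lesions are confirmed by MRI or arthroscopy before consent in both arms, which may keep late ineligibility rare.

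None of this reconciles the OOS exclusion with section {20c}. The Outcomes section already has a per-protocol evaluation of all IMPACT-treated patients, and the exclusion may have been meant for that, but it is not confined to it.

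**Conclusion.** Wrong as written. The OOS exclusion and the intention-to-treat statement contradict each other for the primary outcome. Removal at surgery adds a second loss that, within the 9-month window, can also occur only in the IMPACT arm. The departure from the randomised comparison follows from the text alone and needs no assumption about outcomes.

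A bias in favour of IMPACT is plausible but not established, and its size is unknown. The 0.5–2 point range, against a minimal relevant difference of 10, rests on an assumed 5–20% excluded and an assumed gain of 0 instead of 10. It is larger only if a worse prognosis is also assumed and left unadjusted. A reader might infer a bias of half the target difference, or that replacement itself breaks the randomised comparison. The article supports neither.

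**What to change.** - State that all randomised patients are analysed in their assigned arm for the primary KOOS outcome, including those given an OOS product and those found ineligible at surgery.
- Keep sending these patients the online questionnaires at 3, 6 and 9 months, and say so in sections {11b} and {18b}.
- Report the analysis without them as a labelled per-protocol sensitivity analysis, and reword the OOS section so that its exclusion applies there only.
- For replacement, in either arm, state that a replaced patient stays in the intention-to-treat set with all available data.

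The cost is protocol wording and a few extra online questionnaires through a system already in use. The planned 60 patients and clinical care are unchanged. The price is a primary estimate that may be somewhat less favourable to IMPACT.

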#### Treatment algorithm in case of foreign body response

If there is suspicion of an acute (within 48 h) foreign body response after surgery, a consultation by an independent rheumatologist will be requested immediately. Depending on the severity of the reaction, initial treatment will consist of NSAIDs, anti-histamines, or immunosuppressants. If no improvement occurs within 48 h, treating specialists will consider a diagnostic knee aspiration (in case of signs of infection), anaphylaxis protocol, or debridement and lavage. In case of a late immunological response (after 72 h), infection will be excluded as a cause of the reaction, prior to starting the algorithm as mentioned above.

### Strategies to improve adherence to interventions {11c}

The nonsurgical protocol consists of physiotherapy and/or pain medication and can be adjusted to the individual patient’s needs. The adherence to this protocol will be high as it does not consist of strict guidelines. Adherence to the rehabilitation protocol after IMPACT will be monitored by the specialized physiotherapists in our center. They are in close contact with the treating physiotherapists and monitor progression during study visits.

### Relevant concomitant care permitted or prohibited during the trial {11d}

Concomitant surgery such as anterior cruciate ligament reconstruction or alignment correction is permitted during the trial but will be registered. Injections into the index knee are not permitted 6 months pre- and 12 months postoperatively.

### Provisions for post-trial care {30}

The sponsor has insurance, which is in accordance with the legal requirements in the Netherlands (Article 7 Medical Research Involving Human Subjects Act (WMO)). This insurance provides coverage for damage to research subjects through injury or death caused by any activities of the study. The insurance applies to the damage that becomes apparent during the study or within 4 years after the end of the study.

### Outcomes {12}

The primary outcome is the comparison in total KOOS between patients with cartilage defects that are treated with IMPACT and patients treated with standard care (nonsurgical treatment) until 9 months after randomization. Total KOOS is an average of the scores in the five subscales of KOOS [23]. Other outcomes of interest are outcomes in the five subscales of KOOS, pain (numeric rating scale, NRS), general health (EuroQol five dimensions five levels, EQ5D-5 L), and structural repair (MRI). After 9 months, patients in the nonsurgical group are allowed to undergo IMPACT surgery, this will be regarded as failed nonsurgical treatment, and the time of crossover will be recorded. Change from baseline assessed with the KOOS of the total group of patients treated with IMPACT at 3, 6, 9, 12 and 18 months after treatment will be evaluated (per protocol). The potential effect of time until surgical treatment will be assessed. Clinical safety will be determined by active tracing of the adverse event rate observed after IMPACT and nonsurgical therapy. Additionally, emergence of an immune response will be assessed by screening for anti-HLA antibodies in peripheral blood preoperatively and 4 weeks postoperatively. The HLA phenotype of MSC donors will be compared to newly formed anti-HLA antibodies. Societal costs will be assessed by monitoring the costs related to the IMPACT procedure and the accompanying rehabilitation period, as well as costs related to nonsurgical (or delayed) treatment. In this analysis, two scenarios will be compared: (I) IMPACT vs. nonsurgical treatment and (II) IMPACT vs. delayed surgical treatment. In the first scenario, it is assumed that patients randomized to nonsurgical treatment will not undergo IMPACT in the next 5 years, whereas the second scenario includes patients who were randomized to nonsurgical care and opt for IMPACT after 9 months follow-up. In both scenarios, costs of other healthcare-related resource use (including physiotherapy, home care, medication use, and costs related to adverse events), as well as costs attributable to health-related work leave (i.e., productivity losses), will be collected over a follow-up period of (at least) 9 months. For nonsurgical treatment, health outcomes (from the EQ-5D-5L) and costs within the first 9 months will be extrapolated to calculate costs/QALY over a 5-year time horizon. Similarly, health outcomes and costs for (delayed) IMPACT will also be extrapolated to a five-year time horizon, using results from the completed phase I/II study (unpublished results).

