### Objectives {7}

The current phase III randomized controlled trial explores the efficacy of IMPACT compared to nonsurgical care in 60 patients with large (2–8 cm^2^) articular cartilage defects of the knee. We allow patients in the nonsurgical group to cross-over to the IMPACT group after 9 months of nonsurgical care. Follow-up will be at least 18 months after IMPACT. The primary objective is to compare the Knee Injury and Osteoarthritis Outcome Score (KOOS) at 3, 6, and 9 months follow-up. The secondary objective of this study is to examine morphology and proteoglycan content of repair tissue 6 and 18 months after treatment. Safety endpoints will be determined by the number of (treatment-related) adverse events. In addition, the incremental cost-effectiveness ratio (ICER) of IMPACT vs. nonsurgical care and vs. delayed surgical intervention will be calculated. More specifically, the effect of IMPACT compared with nonsurgical care and delayed surgical intervention in terms of healthcare resource use, productivity losses, and accompanying costs during the study period will be determined and extrapolated to a 5-year time horizon.

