
### Participant timeline {13}

Table 1 shows the participant timeline.

**Table 1 Tab1:** Participant timeline

**Outpatient Clinic:** Screening (MRI) Study information provided in writing	
**Baseline visit:** Informed consent Baseline study MRI Randomization Baseline PROMs	
Group A: IMPACT	Group B: Control (nonsurgical)
**Preoperative screening** Anti-HLA antibodies	**3 months after inclusion** PROMs Check-up study physician (by telephone)
**Surgery/1 day postoperative** Blood chemistry (CRP, ESR, Leucocytes) Visit physical therapist Check-up rheumatologist Check-up study physician	**6 months after inclusion** PROMs Check-up study physician MRI
**1 week postoperative** Blood chemistry (CRP, ESR, Leucocytes) Check-up rheumatologist Check-up study physician	**9 months after inclusion** PROMs
**4 weeks postoperative** Blood chemistry (CRP, ESR, Leucocytes, anti-HLA antibodies) Check-up rheumatologist Check-up study physician	In case of cross-over to IMPACT: follow group A In case nonsurgical treatment is continued: **12 months after inclusion:** PROMs
**3 months postoperative** Check-up study physician (by telephone) PROMs	**18 months after inclusion:** PROMs MRI
**6 months postoperative** Check-up study physician PROMs MRI	
**9 months postoperative** PROMs	
**12 months postoperative** Check-up study physician PROMs	
**18 months postoperative** Check-up study physician PROMs MRI	

*CRP* C-reactive protein, *ESR* erythrocyte sedimentation rat, *HLA* human leukocyte antigens, *IMPACT* Instant MSC Product accompanying Autologous Chondron Transplantation, *MRI* magnetic resonance imaging; *PROMs* patient-reported outcome measures

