## Statistical methods

### Statistical methods for primary and secondary outcomes {20a}

Data will be analyzed using IBM SPSS (version 15.0.0.2, Chicago, IL). Data from the primary objective (KOOS, EQ-5D-5L) will be presented as continuous variables. To compare between the two treatment groups, a mixed model analysis will be performed, with treatment group and assessment date of the PROMs (e.g., baseline, 3 months, 6 months) as fixed factors. Differences will be considered statistically significant for the fixed effect of treatment groups if *p* < 0.05 [30]. The 95% confidence interval of the fixed effect size will be used to assess whether treatment difference reaches the minimally clinical important difference.

T1rho-scores will be calculated from the biochemical MRI scans; differences in T1rho-scores will be compared between the time points *t* = 0 (at inclusion before IMPACT or nonsurgical treatment) and *t* = 6 and 18 months after inclusion or surgery. Differences will be compared using Student’s *t* test. The differences in T1rho-score will be tested for normality using Q–Q plots. *P* values less than 0.05 will be considered significant. We will calculate the ICERs of IMPACT vs. nonsurgical treatment and vs. delayed surgical treatment in terms of cost/QALY over a 5-year time horizon. The effect of uncertainty in input parameters on the ICERs will be calculated by means of one-way sensitivity analysis as well as probabilistic sensitivity analyses using Monte Carlo simulation.

All (S)AE(I)s will be summarized and recorded including the nature, date and time of onset, date of resolution, determination of seriousness, severity, action taken, outcome, and possible causality to study treatment. SAE data will be presented in a descriptive manner.

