### Adverse event reporting and harms {22}

All adverse events reported by the subject or observed by the investigators will be recorded. The causality to the study treatment event will be recorded. Several complications are considered as AEs of Interest (AEIs) based on information from the previous trial and theory of the study procedures: arthralgia, swelling, or crepitation other/longer than may be expected and resulting in alteration in medical care, synovitis, surgical site infection, migration or dislocation of the graft, knee locking, hemarthrosis, arthrofibrosis, chondropathy (including a new cartilage lesion in the same knee or a secondary lesion), general surgery-related disorders (pneumonia, deep vein thrombosis, pulmonary embolism), disorders resulting from general or local anesthesia, and tissue hypertrophy. SAEs will be reported to the CCMO following the CCMO guidelines.

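### Active tracing of adverse events is promised after both treatments, but controls who stay nonsurgical have no scheduled study-physician check-up after 6 months, so side-by-side rates are open to detection bias

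*Protocol article*

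**What the plan says.** **Safety outcome.** Outcomes {12} reads: "Clinical safety will be determined by active tracing of the adverse event rate observed after IMPACT and nonsurgical therapy". Objectives {7} words it as a count: "Safety endpoints will be determined by the number of (treatment-related) adverse events".

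**Capture and analysis.** Adverse event reporting and harms {22} says: "All adverse events reported by the subject or observed by the investigators will be recorded". The statistical methods {20a} list what is recorded for each event, including date of onset, and add: "SAE data will be presented in a descriptive manner". No between-arm test and no exposure denominator is named.

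**Control schedule (Table 1, Participant timeline {13}).** The 3-month entry begins "PROMs Check-up study physician (by telephone" and the 6-month entry is "PROMs Check-up study physician MRI". Then comes "9 months after inclusion PROMs", with nothing further. For patients who do not cross over: "In case nonsurgical treatment is continued: 12 months after inclusion: PROMs". At 18 months these patients have questionnaires and an MRI. Controls who cross over join the IMPACT schedule.

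**IMPACT schedule (Table 1).** Study-physician check-ups fall at day 1, week 1, week 4, 3 months (telephone), 6, 12 and 18 months. A rheumatologist also sees the patient at day 1, week 1 and week 4. The 9-month entry is questionnaires only, as for controls.

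**The concern.** Active tracing means that somebody asks. After 6 months nobody is scheduled to ask a continuing control about adverse events, whereas an IMPACT patient is seen twice more. Several of the events of interest in section {22}, such as arthralgia, swelling, locking and chondropathy including a new lesion, can arise without surgery. The control rate therefore carries information, and it is the one likely to be under-recorded.

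Two rates reported within one safety outcome will be read against each other. A higher rate after IMPACT could then reflect more harm or more asking, and the data could not separate the two. Section {12} also enters adverse event costs in both economic scenarios, so uneven capture could carry into an analysis that is explicitly comparative. A statistical analysis plan can supply a person-time denominator, but it cannot recover events that were never elicited.

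**Working it through.** The documents give no safety figure to reproduce, so the check is a count of Table 1 followed by an exposure calculation.

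**1. Scheduled study-physician check-ups**

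| Period | IMPACT | Control staying nonsurgical |
|---|---|---|
| Day 1, week 1, week 4 | 3 | 0 |
| 3 months (telephone) | 1 | 1 |
| 6 months | 1 | 1 |
| 9 months | 0 | 0 |
| 12 months | 1 | 0 |
| 18 months | 1 | 0 |
| **Total to 9 months** | **5** | **2** |
| **Total to 18 months** | **7** | **2** |

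Counting the three rheumatologist checks separately gives 8 versus 2 to 9 months and 10 versus 2 to 18 months. Removing the perioperative checks gives 5 − 3 = 2 versus 2 to 9 months. The imbalance that is not perioperative is 2 versus 0, and all of it falls at 12 and 18 months.

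**2. Time after the last check-up**

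- Continuing control: (18 − 6)/18 = 67% of follow-up.
- Within the first 9 months: (9 − 6)/9 = 33%, in both arms alike. An IMPACT patient can still be asked about months 6 to 9 at the 12-month check-up; a continuing control has no such later visit.

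**3. What two extra check-ups could do (illustration only)**

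Assume that an event arising between 6 and 12 months is not volunteered, and that each later check-up elicits it independently with probability q. The documents give no value for q. The chance of recording it at a check-up is 1 − (1 − q)² after IMPACT and 0 for a continuing control:

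- q = 0.2: 1 − 0.8² = 36% versus 0.
- q = 0.5: 1 − 0.5² = 75% versus 0.

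This ignores the 18-month MRI, which both groups have.

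**4. Exposure behind raw counts**

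Inputs: 60 patients allocated 1:1, so 30 per arm (sections {8} and {14}); at least 18 months of follow-up after IMPACT (section {7}), taken as exactly 18. Assumptions: crossover at exactly 9 months, in a fraction c of controls. The documents do not give c.

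- Nonsurgical patient-months = 30 × [9c + 18(1 − c)]
- IMPACT patient-months = 30 × 18 + 30c × 18

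| c | Nonsurgical | IMPACT | Ratio |
|---|---|---|---|
| 0% | 540 | 540 | 1 |
| 50% | 405 | 810 | 2 |
| 100% | 270 | 1080 | 4 |

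Over the first 9 months from randomisation, exposure is 30 × 9 = 270 patient-months in each arm, whatever c is.

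**The case against.** The strongest reply is that the protocol never says adverse events will be compared. Serious events are described, and the abstract and discussion speak of the safety of IMPACT itself, in 30 to 60 patients. This stands. A reader might infer a planned between-arm test that is biased; the documents support only two reported rates that are open to bias if set side by side.

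Second, 5 versus 2 looks like a gross imbalance within the randomised period. It is not. The three extra checks belong to surgery, have no control counterpart and cannot pick up an event that starts after week 4. The gap from 6 to 9 months is shared. Many events of interest, such as graft migration or anaesthetic complications, cannot occur in controls at all.

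Third, the fourfold exposure ratio needs every control to cross over. With none, exposure is equal. Section {12} speaks of a rate, and crossover time and event onset are both recorded, so patient-time can be derived and the choice of denominator may properly sit in an analysis plan. That answers the exposure point but not the detection point.

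Fourth, one might conclude that late control events would be known only if volunteered. That is too strong. Continuing controls have an MRI at 18 months, which could show chondropathy or a new lesion. The medical consumption questionnaire may signal care sought, and researchers contact patients where needed, though section {18b} describes that contact as serving questionnaire completion. None of these is structured questioning about adverse events.

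Finally, this article condenses a fuller protocol, which may hold adverse event items at the questionnaire time points. That cannot be judged here. If it does, the point falls away.

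**Conclusion.** The point holds in a limited form. The promise of active tracing after both treatments does not fit a schedule in which continuing controls have no study-physician check-up for 12 of 18 months, while IMPACT patients have two in that time. Up to 9 months the schedules differ only by three perioperative checks.

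The likely direction is under-recording of late, non-serious events under continued nonsurgical care. Its size cannot be derived from the documents, because neither the crossover share nor the chance of eliciting an event at a check-up is given. The exposure ratio of 1 to 4 rests on the assumptions stated above, and matters only if raw counts are set side by side.

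This does not touch the primary KOOS analysis. It is a cheap improvement to a descriptive safety outcome, worth making because events that were never asked about cannot be recovered later.

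**What to change.** - **Ascertainment.** Add one short structured set of adverse event questions, with the same recall period, to the online survey at 3, 6, 9, 12 and 18 months in both arms. Have the study team follow up positive answers.
- **Between-arm summary.** Restrict any such summary to events from randomisation to 9 months captured at these common time points. Give both the number of patients with at least one event and events per patient-month. State one time origin, since Table 1 dates IMPACT visits from surgery and control visits from inclusion.
- **Separate reporting.** Show events found only at the perioperative visits, and events after crossover, separately by treatment received.
- **Wording.** Align the count in section {7} with the rate in section {12}.

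Cost: a slightly longer questionnaire, some call-backs and a protocol amendment during recruitment; no added visits. Ten patients had been included by 15 May 2020. Those already past a given time point should be flagged as assessed under the earlier method, so that the change in ascertainment is visible in the report.
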